### Methods for additional analyses (e.g., subgroup analyses) {20b}

There are no sub-group analyses planned.

### Methods in analysis to handle protocol non-adherence and any statistical methods to handle missing data {20c}

In this trail, protocol adherence will be defined as attending at least four CBT sessions and responding to at least one post-baseline measurement (T2-3). The therapist will document each session in the medical journal.

Missing data will be addressed through multiple imputation by chained equations (fully conditional specification) with predictive mean matching. The imputation model will include auxiliary information from measurements of the efficacy variable of interest collected at previous and subsequent visits. A total of 50 imputed data sets will be generated, and the results pooled according to Rubin’s rules.

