### Participant timeline {13}

#### Sample size {14}

The power calculation is based on an expected reduction in the symptoms of GD, measured by IGDS9-SF. While the IGDS9-SF demonstrates robust psychometric properties [28, 39], we have not found any clinical studies using this instrument as an outcome measure after intervention. However, in our pilot study [24] we included a set of items highly resembling the IGDS9-SF and observed a mean decrease of 10.9 (SD 10.6) points. There was no wait list control in the pilot study, but there was a waiting time between first visit and start of treatment. During this time, we saw a small mean decrease of 0.5 on the same symptom measure. Based on this, we would not expect any or a very small reduction in the wait list control group. However, in the RCT the control group will receive questionnaires including questions about time spent gaming. This kind of self-monitoring might lead to some additional changes in behavior that would occur while waiting for treatment.

Based on our pilot data [24], we have therefore concluded that a reasonable assumption is a 10-point reduction in the intervention group and a 5-point reduction in the control group. Hence, we calculated the sample size to be able to detect a difference of 5 points between the groups. With a standard deviation of 10, power of 80 percent and significance level of 5 percent, the required group size is 64 individuals per arm or 128 individuals in total. Assuming a drop-out rate of 20 percent, approximately 160 individuals would need to be recruited.

A 5-point difference on the IGDS9-SF scale corresponds to changes in frequency of at least two symptoms of GD. It is also equivalent to the minimal clinically important difference defined as half the standard deviation of the change scores[40]. Due to the lack of clinical evidence using this particular questionnaire, we have also made parallel calculations of sample size using data about time spent gaming. The sample size (128 individuals) would allow for detection of about an eight hour decrease in time spent gaming per week, i.e. a full workday. Based on clinical judgment and data from our pilot study, we have therefore made the decision that this sample size would allow for detection of clinically meaningful changes.

Power was calculated based on an independent samples t-test for two groups, that is, the Student’s t-test. Calculations were performed using the pwr.t.test from the pwr r-package.

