## Data collection and management

### Plans for assessment and collection of outcomes {18a}

Several self-report questionnaires and semi-structured diagnostic instruments will be used in this trial.

Data will be collected digitally at several time-points before, during and after the intervention (see Table 2 Timeline). For patients who are not able to access the digital questionnaire service, it will be possible to fill out the questionnaires on paper.

The first assessment will be done before the initial visit to the clinic (T0). The second will occur right before the start of treatment (T1). Measurements will continue through the treatment period with questionnaires distributed at session four (T2) and nine (end of treatment) (T3). If the treatment takes longer than expected an extra measurement will occur during the treatment period.

The participants will be followed up by telephone three months after the end of treatment. In a subsequent study, the participants will also be followed up after 6, 12, 18 and 24 months, with the same questionnaires as in the study described in this protocol.

The primary outcome measure is:

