#### Gaming Disorder Timeline Follow-Back (GD-TLFB)

This gaming-related diary is the third main outcome measure. It was originally developed to track alcohol-consumption and has been adapted to measure gaming behavior [43]. The adapted version collects measurements on a weekly basis: number of days gaming, total hours of gaming and leisure time without screen (e.g., reading a book, meeting friends, or exercising). The diary will be filled out weekly during treatment to evaluate the process. It will also be used as a visual tool for the participants to gain an overview of their gaming habits. The control group will also fill out the gaming diary during the control period.

Exploratory outcomes are:

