## Statistical methods

### Statistical methods for primary and secondary outcomes {20a}

Descriptive data will be presented by treatment arm and, where applicable, by timepoint. For numeric variables, summary statistics will include the number of available and missing measurements, mean, standard deviation (SD), median and minimum and maximum values. Treatment comparisons for primary, secondary and exploratory endpoints will be conducted using analysis of covariance (ANCOVA), adjusted for baseline values.

The primary efficacy analysis, which assesses the change in IGDS9-SF from baseline to 12 weeks between the CBT and control groups, will be conducted using analysis of covariance, adjusted for baseline values, with missing data handled through multiple imputation using predictive mean matching. The treatment effect will be tested at a significance level of α = 0.05. Results will be reported as the mean difference with 95% confidence intervals.

Secondary efficacy analyses of changes in GDT and GD-TLFB from baseline to 12 weeks between the CBT and control groups will be conducted using the same methodology as the primary efficacy analysis. To control the overall Type I error rate for secondary endpoints, an alpha-splitting testing procedure will be employed. The two secondary endpoints—GD-TLFB weekly hours and changes in GDT scores from baseline to 12 weeks—will initially be tested with an alpha level of 0.025 each. If the first test (i.e., GD-TLFB) demonstrates statistical significance, the entire probability mass will be transferred to the next secondary endpoint (i.e., GDT), which will subsequently be tested at the 0.05 significance level, with results reported as the mean difference and corresponding 95% confidence intervals.

All statistical tests will be two-tailed, with results presented as mean differences and accompanied with corresponding 95% confidence intervals.

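### For CBT patients who stop before session four and are not reached later, the stated imputation model carries no information on treatment exposure and borrows T3 mostly from patients who continued

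*Protocol article*

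**What the plan says.** The primary analysis (section {20a}) is a baseline-adjusted ANCOVA of the change in IGDS9-SF to 12 weeks, with missing values filled by multiple imputation using predictive mean matching. Section {20c} names the auxiliary variables: "The imputation model will include auxiliary information from measurements of the efficacy variable of interest collected at previous and subsequent visits". It mentions neither sessions attended nor stopping of treatment, and it does not say whether imputation is done by arm.

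On timing, section {18a} says: "Measurements will continue through the treatment period with questionnaires distributed at session four (T2) and nine (end of treatment) (T3".

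Three other provisions bear on the point:
- Section {18b} plans to telephone anyone who discontinues, whatever the reason, and to obtain answers equivalent to the T3 questionnaires. It gives no timing for the call.
- IGDS9-SF is collected from T0 to T4 (its description under {18a}), so T4 is a later visit open to the model.
- Exposure is recorded. On sessions, {20c} says: "The therapist will document each session in the medical journal". On gaming hours, the GD-TLFB description says: "The diary will be filled out weekly during treatment to evaluate the process". The control group keeps the same diary.

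**The concern.** Take a CBT patient who attends one to three sessions, stops, and gives no T2, no telephone T3 and no T4. The model then knows only that patient's T0 and T1. Predictive mean matching looks for donors with similar early scores, and within the CBT arm most donors went on with treatment. The imputed T3 is right only if stopping early says nothing about outcome once the early scores are known.

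The protocol gives reasons to doubt that:
- Its adherence definition ({20c}) starts at four sessions.
- The pilot behind the 10-point assumption is described in the Discussion as 20 participants who took part in at least four sessions. No data in the document therefore support the same benefit for people who stop earlier.
- The reasons for discontinuing in {11b} include serious adverse events, such as significant psychiatric worsening, and personal crises. These are plausibly related to outcome.

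If early stoppers do worse than continuers, the error favours CBT in the primary comparison and grows with the number of unreached stoppers.

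**Working it through.** **The plan's own figure.** Section {14} assumes that "a reasonable assumption is a 10-point reduction in the intervention group and a 5-point reduction in the control group", a difference of 5, and states: "With a standard deviation of 10, power of 80 percent and significance level of 5 percent, the required group size is 64 individuals per arm". A two-sided t-test with standardised difference 5/10 = 0.5, alpha 0.05 and power 0.80 gives 63.77, so 64 per arm (power 80.1%). Then 128/(1 − 0.20) = 160, or 80 per arm. The figure reproduces.

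**Assumptions that are not in the document.**
- s: share of the CBT arm stopping before session four, with no T2.
- r: share of those stoppers with T3 obtained by telephone.
- g: stoppers' true gain over control, in points.
- Imputation is by arm, T4 is missing for stoppers, and everyone else is observed.

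**Formulas.**
- True all-randomised difference: (1 − s)·5 + s·g.
- Imputed difference (unreached stoppers receive the mean of observed CBT patients, including reached stoppers): [(1 − s)·5 + s·r·g] / [(1 − s) + s·r].
- Overstatement, by subtraction: s(1 − s)(1 − r)(5 − g) / [(1 − s) + s·r].

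**Example.** With s = 0.20, r = 0.30, g = 0, the true difference is 4.00. The imputed difference is 4.00/(0.80 + 0.06) = 4.65, so the overstatement is 0.65.

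**Overstatement in points, g = 0 (stoppers do as controls do).**

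| s | True | r = 0 | r = 30% | r = 50% | r = 80% |
|---|---|---|---|---|---|
| 10% | 4.50 | 0.50 | 0.34 | 0.24 | 0.09 |
| 15% | 4.25 | 0.75 | 0.50 | 0.34 | 0.13 |
| 20% | 4.00 | 1.00 | 0.65 | 0.44 | 0.17 |

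The overstatement is proportional to 5 − g, so every entry halves if stoppers keep half the benefit (g = 2.5).

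**Check by simulation.** Chained equations with predictive mean matching over T0 to T4 were run at 80 per arm, with 150 trials per row, 5 imputations and s = 20%. The full-data figure varies around 4.00 because each row is a separate set of trials. The standard error of each excess is 0.02 to 0.05.

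| Imputation | T3 reached | T4 obtained | Full data | Imputed | Excess |
|---|---|---|---|---|---|
| By arm | 0 | 0 | 3.88 | 4.98 | 1.10 |
| By arm | 50% | 0 | 4.02 | 4.47 | 0.45 |
| By arm | 80% | 0 | 4.02 | 4.18 | 0.16 |
| By arm | 0 | 50% | 4.23 | 4.86 | 0.63 |
| Arm as predictor | 0 | 0 | 4.04 | 4.76 | 0.72 |
| Arm left out | 0 | 0 | 3.96 | 4.35 | 0.39 |

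The direction is the same under all three structures. T4 reduces the error without removing it.

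**Effect of an exposure indicator.** In a further simulation of 1,000 trials per cell, with s = 20% and r = 30%, the full-data difference was 4.05. The stated model gave 4.69, and adding a stopped-early indicator gave 4.21. The residual was therefore 0.16, against 0.64 before. A second run at r = 30% and s = 10–20% left 0.15–0.18. The reason is how few stoppers are reached: with s = 10% and r = 30%, 80 × 0.10 × 0.30 = 2.4 patients inform the indicator. With eight stoppers, the chance that none is reached is 0.7^8 = 0.058.

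**The case against.** A reader might infer that the plan imputes every early stopper from pre-treatment scores and so credits them all with a full course. The document does not support that:
- Section {18b} makes imputation the fallback for discontinuers who are not reached. Those who are reached have a real T3 and also serve as donors.
- The stated model includes later visits, so T4 counts where it exists.
- Full credit (5.00 imputed against 4.00 true at s = 20%) needs no T3 and no T4 from any stopper, and imputation by arm, which the protocol does not state.

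That a stopper has no T2 is also an inference. Questionnaires are digital, staff send reminders ({11c}), and the waitlist arm is assessed at the same time points without sessions. T2 may therefore still be sent. The timeline table is not legible in the text at hand, so this cannot be settled.

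It can also be said that the section lists what the model will include, not all it may include, and that an SAP may add predictors, by-arm imputation or sensitivity analyses. That is fair, and a missing sensitivity analysis is not part of this point. What stands is narrower. The protocol does choose a class of auxiliary variables, that class carries no exposure information, and better variables are already collected.

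Finally, the rates are assumed. Section {14} gives 20% overall drop-out, not drop-out before session four, so s = 20% is a high case. The simulated standard deviation of the estimate is about 1.1 points, so the bias is smaller than the sampling error. It is nevertheless systematic and favours CBT.

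**Conclusion.** The point holds for a limited group: CBT patients who stop before session four and give no T2, no telephone T3 and no T4. For them the stated model uses only earlier scores on the same questionnaire and draws T3 mostly from patients who continued. If they do worse than continuers, the primary difference is overstated.

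With 10–20% early stoppers doing as controls do and 30–50% reached, the overstatement runs from 0.24 of a true 4.50 (5%) to 0.65 of a true 4.00 (16%). High telephone retrieval, retained benefit and T4 data each shrink it, and with near-complete retrieval it is negligible. The three driving rates are assumptions, so this is a range and not an estimate for this trial. The change is worth making because it uses data already collected and acts on the primary result.

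**What to change.** State in {20c}, or in the SAP before analysis, that:
1. imputation is done separately by arm;
2. in both arms the model for IGDS9-SF also includes weekly gaming hours from the diary, both early-week and last-available values;
3. in the CBT arm it also includes the number of sessions attended, or an indicator of stopping before session four.

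The cost is some imputation code, with no new data collection. The estimate may become less favourable to CBT. Its variance rises slightly: in one simulation at 20% stoppers its standard deviation went from 1.15 to 1.24. The change reduces the bias without removing it. When few stoppers are retrieved, about 0.15–0.18 points may remain, so the telephone follow-up in {18b} is still the main protection.

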### Plans to give access to the full protocol, participant level-data and statistical code {31c}

The data sets used and/or analyzed during the current study can be made available by the corresponding author upon reasonable request.

## Oversight and monitoring

### Composition of the coordinating center and trial steering committee {5d}

To handle day-to-day trial conduct, a trial management group is organised, composed of two researchers connected to the clinic. They attend the weekly clinical meetings together with the therapists. The purpose of these meetings is to review participant progress and clinical concerns (e.g. AEs), ensure consistency in the CBT-treatment and adherence to the protocol, and address problems related to the implementation of the treatment. These meetings contribute to the overall trial quality and support effective team coordination. Clinicians participating in the trial will be responsible for participant recruitment, delivery of the intervention and data collection.

There is also a trial steering committee that will meet at regular intervals and is responsible for monitoring the progress of the trial, ensuring compliance with the protocol, reviewing information from related studies, communicating updates to relevant stakeholders, and advising on the publicity and presentation of all aspects of the trial.

### Composition of the data monitoring committee, its role and reporting structure {21a}

N/a. The present study is judged as a low-risk trial, not involving any medications or medical equipment.

### Adverse event reporting and harms {22}

In this trial, adverse events (AEs) refer to any untoward occurrence in a study participant, regardless of its relationship to the intervention (e.g. worsening of psychiatric symptoms). Serious adverse events refer to e.g. hospitalization, suicide attempts or significant worsening of psychiatric symptoms requiring extensive additional out-patient care.

The therapists meet the participants once every week and will have adequate opportunities to detect AEs. The questionnaires about psychiatric symptoms during treatment will also be used to collect information about AEs, such as worsening of psychiatric symptoms. The Negative Effects Questionnaire used at the end of treatment will also assist in identifying AEs, as well as the follow-up assessments at three months after treatment. Adverse event data from questionnaires will be systematically collected by a designated member of the research team at each scheduled assessment.

Adverse events identified by the therapist or spontaneously reported will be registered in the eCRF of the trial dataset and reported during the weekly clinical meetings. The severity of the adverse event will be evaluated by the trial management group. The management will depend on the level and nature of the adverse event. In occurrence of an AE or SAE, the participant will be referred to relevant care. Further, SAEs will be registered in the internal reporting system at the hospital and reviewed by a psychiatrist who makes decisions about if the event should be reported and investigated by the national Health and Social Care Inspectorate. Serious adverse events will also be reported to the ethical review board. All collected adverse event data will include onset, duration, severity, relationship to the intervention, expectedness and outcome in accordance with the CONSORT harms statement 2022 [61].

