#### Intervention group

##### CBT manual

The main part of the intervention is based on a CBT manual comprising nine different modules, each addressing an area identified as problematic for a majority of this patient group, for example, “Making gaming more difficult” (to address problems associated with diminished control over gaming) and “Emotions” (because gaming often serves as a dominant strategy to regulate emotions) (see Table 1). In addition to the main modules, there will also be three optional modules with content valid for some of the participants. Every participant will have an individual treatment plan, including the main and optional modules corresponding to individual needs and difficulties related to gaming. Based on clinical judgment, the length and number of modules may therefore differ between patients.

**Table 1 Tab1:** Modules included in the CBT manual

Module	Content
1	Goal setting
2	Understanding your gaming
3	Planning of time
4	Making gaming more difficult. Mid-treatment assessment
5	Alternative activities
6	Procrastination
7	Emotions
8	Thoughts
9	Relapse prevention. Post-treatment assessment
Optional	Support for home assignments
Optional	In-game purchases
Optional	Handling obstacles

The sessions are planned for a duration of between 45 to 60 min. During each session, the psychologist will review last week's homework together with the participant and present a new topic. If more time is needed for last week’s topic, this will be accommodated. In between every session the participants will work on take home assignments related to the different topics.

To ensure treatment fidelity over time, the therapists will document which parts of each module have been covered in the session.

The treatment will last for approximately 12 weeks, with one session every week, and will be led by clinical psychologists with good experience in CBT. Assessments will be made at the first, fourth and last session (T1, T2 and T3, see Table 2, Timeline).

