#### Control group

Participants allocated to the control group will be put on a waitlist for approximately 12 weeks. The participants in the control group will be distributed the same questionnaires and gaming diary at the same time points as the intervention group (see Table 2, Timeline). After the waitlist period, the participants in this group will be offered the same treatment as the intervention group.

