## Discussion

The aim of the present study is to evaluate the effect of CBT on symptoms of GD. Cognitive behavioral therapy involves managing problematic thoughts, feelings and behaviors in more functional ways and thereby reducing symptoms. Cognitive behavioral therapy has previously been reported to have good effects in the treatment of other behavioral addictions (e.g., gambling disorder) [62]. Data from our pilot study, which included 20 participants who participated in at least four sessions using the CBT manual described in this protocol, showed a significant decrease in symptoms of GD, as well as a large reduction in weekly hours of gaming [24]. Due to these promising results, we will now implement the manual in a high-quality RCT with a waitlist control and a three-month follow-up.

The trial is carefully planned, taking into account many possible pitfalls. However, the present study has some limitations: First, and most important, the time for completion of the study is highly dependent on the rate of referral to the clinic. A regular inflow of participants is crucial to keep the timeline intact. Also, participants randomized to the control group will have to wait 12 weeks before starting the treatment, with a risk of increased impairments during the waitlist period. The choice of a waitlist control condition could also be considered a limitation but has been chosen as there is no better option or gold standard treatment to use as a comparison.

The study also has several practical implications and strengths. It is a clinical study, implemented at an established clinic that specializes in the treatment of gambling and gaming disorders. The inclusion criteria mirror the typical patients seeking treatment for GD, as psychiatric co-morbidity is common in this group. The inclusion of patients with psychiatric co-morbidity makes the results from the study applicable in clinical practice. To enable inclusion of patients with different levels of functioning, the study design allows adjustments based on individual needs, while still using a structured and well-described manualized intervention. Given the worldwide increase in gaming [63] there will be a need for treatment of GD in the health care sector, as well as increased awareness and preventive strategies in non-medical settings that encounter at-risk individuals. This trial will contribute valuable information about patients with GD and treatment outcomes.

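### Adverse-event detection is justified by weekly therapist meetings that only the CBT arm has, so events missed by the shared questionnaires are ascertained unequally between the arms

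*Protocol article*

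**What the plan says.** The section on adverse event reporting and harms {22} defines an AE as any untoward occurrence, whether or not it is related to the treatment. It supports detection with this sentence: "The therapists meet the participants once every week and will have adequate opportunities to detect AEs".

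The section names further routes:

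- Symptom questionnaires: "The questionnaires about psychiatric symptoms during treatment will also be used to collect information about AEs".
- The Negative Effects Questionnaire (NEQ).
- The follow-up three months after treatment.
- Spontaneous reports.
- A general collection rule that names no arm: "Adverse event data from questionnaires will be systematically collected by a designated member of the research team at each scheduled assessment".

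The weekly contact is described under the intervention group, in the CBT manual section: "The treatment will last for approximately 12 weeks, with one session every week". For the other arm, the control group section says: "Participants allocated to the control group will be put on a waitlist for approximately 12 weeks". It adds: "The participants in the control group will be distributed the same questionnaires and gaming diary at the same time points as the intervention group". No session, call or visit is described for the waitlist period. The Discussion names the waitlist as a limitation, "with a risk of increased impairments during the waitlist period".

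**The concern.** The sentence on weekly meetings speaks of the participants in general, yet it is true of only one arm during the controlled period. Because AEs are defined regardless of cause, they should be looked for in the same way in both arms. If one arm has an extra detection route every week, by-arm counts mix true incidence with opportunity to detect.

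Two things are at stake. CBT may appear to carry more AEs than waiting merely because someone asks. And events on the waitlist may go unrecorded in the period for which the protocol itself names a risk of deterioration. The protocol has no data monitoring committee and plans no auditing, so no other described mechanism would make up for the gap.

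**Working it through.** **Step 1. Routes by arm during the roughly 12-week comparison**

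| Route | CBT | Waitlist |
|---|---|---|
| Weekly therapist meeting | yes | none described |
| Family sessions with a social worker | 3–4 offered | none described |
| PHQ-9, GAD-7, IGDS9-SF, GDT | every time point | same time points |
| NEQ | yes | asks about effects of psychological treatment, so no equal route |
| Spontaneous report | open | open |

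The adherence section {11c} urges participants to contact the clinic about problems, but words this for the treatment period. The symptom-questionnaire sentence in {22} is likewise worded for treatment. The control group section and the general collection rule indicate that the questionnaires nevertheless serve both arms.

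**Step 2. What the shared questionnaires can and cannot find**

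- PHQ-9 and GAD-7 look back two weeks. After T1 they fall at T2 and T3 within the comparison, so they cover about 2 × 2 = 4 of the 12 weeks.
- IGDS9-SF and GDT are adapted to look back four weeks, so they cover up to 2 × 4 = 8 of the 12 weeks, for gaming symptoms only.
- All four are symptom scales. They do not record a hospital admission, which is one of the protocol's own examples of a serious event.

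The unequal part is therefore events outside these scales and worsening between assessments.

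**Step 3. Possible size**

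The document gives no AE rate and no detection rate, so there is no harms figure to reproduce. The planned sample size does reproduce: for a 5-point difference, SD 10, 80% power and two-sided 5%, the t-test solution is 63.77, hence 64 per arm and 128 in total; 128 / (1 − 0.20) = 160. With 1:1 allocation that is about 80 per arm.

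Assumptions (none from the document):

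- the true risk *p* is equal in both arms;
- the shared routes find a share *q* of events in each arm;
- the therapist finds a share *t* of the events that the shared routes miss, in the CBT arm only.

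Formulas:

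- recorded risk, waitlist = *p* × *q*
- recorded risk, CBT = *p* × [1 − (1 − *q*)(1 − *t*)]
- recorded risk ratio = [1 − (1 − *q*)(1 − *t*)] / *q*, in which *p* cancels

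| *q* | *t* = 0.5 | *t* = 0.8 |
|---|---|---|
| 0.3 | 0.65 / 0.3 = 2.17 | 0.86 / 0.3 = 2.87 |
| 0.5 | 0.75 / 0.5 = 1.50 | 0.90 / 0.5 = 1.80 |
| 0.7 | 0.85 / 0.7 = 1.21 | 0.94 / 0.7 = 1.34 |
| 0.9 | 0.95 / 0.9 = 1.06 | 0.98 / 0.9 = 1.09 |
| 1.0 | 1.00 | 1.00 |

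In counts, with *p* = 0.20, *q* = 0.5 and 80 per arm, the waitlist records 80 × 0.20 × 0.5 = 8.0 events. CBT records 80 × 0.20 × 0.75 = 12.0 to 80 × 0.20 × 0.90 = 14.4, although the true number is 16 in each arm.

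**The case against.** A reader might infer that AE detection rests on therapist contact alone, and that psychiatric worsening on the waitlist goes unseen. The document does not support that. The main symptom scales go to both arms on one schedule, and a designated team member collects questionnaire AE data at each assessment. Worsening of psychiatric symptoms is the protocol's own example of an AE, and depression and anxiety have a shared route at those assessments. This part of the objection stands and narrows the point to the events identified in Step 2.

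A reader might also infer that a planned harms comparison is biased by a known amount. The article specifies no such comparison: the treatment comparisons in {20a} are for the primary, secondary and exploratory endpoints, and otherwise descriptive data are presented by arm. How harms are tabulated may properly be left to the analysis plan. A statement such as a two-fold excess would only restate whatever detection ratio was assumed. This stands too: what the text supports is a risk of unknown size to any by-arm harms reporting.

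Finally, unequal contact is inherent in a waitlist design, which the protocol justifies and lists as a limitation. That explains why therapists do not see the waitlist. It does not make the sentence about weekly meetings true of that arm, nor does it prevent the same AE question from being put to both arms.

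**Conclusion.** The point holds in a limited form. The stated ground for adequate detection applies to the CBT arm only. Ascertainment is alike for what the shared scales measure at the assessments, and unequal for other events and for worsening in between. Any by-arm AE counts therefore risk over-counting in CBT and under-detection on the waitlist.

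The direction is clear provided that the shared routes work equally well in both arms and the therapist only adds to them. The size cannot be computed from the document. Over the assumed ranges (*q* 0.3 to 0.9, *t* 0.5 to 0.8, equal true risk) the recorded risk ratio runs from about 1.06 to 2.87. The low end is near negligible and the high end would mislead. The primary efficacy analysis is not affected.

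**What to change.** 1. Limit the sentence on weekly meetings in {22} to participants in treatment.
2. Add one identically worded AE question, covering hospitalization and other serious events, to the questionnaires that both arms already receive at T2 and T3. Let it ask about the time since the previous assessment, so that the intervals between assessments are covered. The research-team member already designated in {22} collects the answers.
3. Record the source of every event: common question or questionnaire, therapist, NEQ, or spontaneous report.
4. Report all AEs and serious AEs by arm with the source shown. Base any between-arm comparison of AE frequency on the commonly elicited events, and show therapist-detected and NEQ events separately. Keep all serious events, including those reported spontaneously, in the by-arm table; spontaneous report is the likely route for them on the waitlist.

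The existing assessments are a better place for the question than the weekly diary. The diary ("The control group will also fill out the gaming diary during the control period") is a secondary outcome and a treatment tool, and the sample size section already warns that self-monitoring may change behaviour in the control group. The review load is also smaller: at most 160 × 2 = 320 answers, against 160 × 12 = 1,920 for a weekly item.

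The cost is one extra question per assessment and its review. No treatment, endpoint or sample size changes. Some imbalance will remain, since answers rely on recall and therapist contact may prompt it in the CBT arm. The Trial status section gives recruitment as still to start; events missed during the waitlist cannot be fully recovered later.
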